### Data analysis

Data analysis will be performed by the SPSS 26.0 statistical software, and statistical analysis of efficacy will be based on intention-to-treat analysis (ITT) principles.We will check whether the data is normally distributed using the Shapiro Wilk normality test. Nonparametric analysis such as chi-square test will be applied for the count data, and it will be expressed as rate or composition ratio. Nonnormal data will be tested using the Kruskal–Wallis test.Paired *t*-tests will be used for pre- and post-treatment comparisons of groups, one-way ANOVA for inter-group comparisons, and Bonferroni correction for post hoc comparisons between groups.Two-factor repeated measures ANOVA will be employed to investigate the impact of within-group factors (time points) and between-patient factors (subgroups) on outcomes and to analyze main and interaction effects.Pearson correlation analysis will be performed to investigate the correlation between cortical excitability (latency and CMCT) and motor function (FMA), the relationship between serum factors (BDNF, proBDNF, and MMP-9) and motor function, and the correlation between cortical excitability and serum factors.

A *P* value of < 0.05 will be regarded as statistically significant.

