**Methods:**

Seventy-six subjects will be randomly divided into combined, low-frequency, high-frequency, and control groups based on the proportion of 1:1:1:1, with 19 cases in each group. All groups will have conventional rehabilitation, on top of which the combined group will receive 1 Hz rTMS in the unaffected hemisphere and 10 Hz rTMS in the affected hemisphere. The low-frequency group will be administered 1 Hz rTMS in the unaffected hemisphere and sham stimulation in the contralateral hemisphere. The high-frequency group will be administered 10 Hz rTMS in the affected hemisphere and contralateral sham stimulation. The control group will receive bilateral sham stimulation. Assessments will be performed at baseline, after 2 weeks of treatment, and at post-treatment follow-up at week 6. The primary outcomes are FMA-UE (Fugl-Meyer assessment-upper extremity), latency, and serum BDNF levels. The secondary outcomes are the National Institute of Health Stroke Scale (NIHSS), Brunnstrom staging (BS), modified Ashworth scale (MAS), Modified Barthel Index (MBI), central motor conduction time (CMCT), precursor proteins of mature BDNF (proBDNF), and matrix metalloproteinase-9 (MMP-9) levels. Adverse events, such as headaches and seizures, will be recorded throughout the study.

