This trial aims to investigate the clinical efficacy of LF-HF-rTMS on upper extremity motor function in convalescent stroke patients and to explore the mechanisms underlying its therapeutic effects. This study will assess the following: significant changes in clinical behavioral assessments and cortical excitatory parameters in patients with convalescent stroke after 10 interventions with rTMS, compared with that by sham and unilateral hemispheric stimuli. In addition, we will measure the concentrations of neuroplasticity mediators, serum BDNF, pro-BDNF, and MMP-9, and analyze their correlation with behavioral improvement.

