## Methods

### Study design

This is a prospective, single-blind, randomized controlled clinical trial with hidden assignment and intent-to-treat analysis. We will recruit 76 patients with upper extremity motor deficits after stroke in convalescence and then randomly and equally assign them to LF-HF-rTMS, low-frequency, high-frequency, and sham stimulation groups. Subjects will be assessed for clinical behavior, neurophysiology, and serologic testing at baseline and after 2 weeks; further follow-up assessment of clinical behavior will be performed after 6 weeks (Fig. 1).

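### A normality test on the trial data picks the between-group test; the rank fallback's link to the pairwise and repeated-measures steps is unclear, and no branch names a baseline covariate

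*Protocol article*

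**What the plan says.** All of the relevant text is in the Data analysis section of the Protocol article, except the trial question and the outcomes.

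- Gate: "We will check whether the data is normally distributed using the Shapiro Wilk normality test".
- Fallback: "Nonnormal data will be tested using the Kruskal–Wallis test".
- Parametric comparison: "one-way ANOVA for inter-group comparisons, and Bonferroni correction for post hoc comparisons between groups", next to paired t-tests within groups.
- Longitudinal step: "Two-factor repeated measures ANOVA will be employed to investigate the impact of within-group factors (time points) and between-patient factors (subgroups) on outcomes". Its stated targets include the group-by-time interaction. No normality condition is attached to it.
- Question (Background, last paragraph): change with the combined regimen "compared with that by sham and unilateral hemispheric stimuli".
- Outcomes (Abstract, Methods): "The primary outcomes are FMA-UE (Fugl-Meyer assessment-upper extremity), latency, and serum BDNF levels". All are measured at baseline and 2 weeks. At the later visit, "further follow-up assessment of clinical behavior will be performed after 6 weeks", so of the three primary outcomes only FMA-UE has a third time point.

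**The concern.** The between-group method for a primary outcome is not known until the outcome data have been tested, and it may differ between outcomes and visits. The rule is also incomplete. The variable tested, the level (arm or whole sample), the use of raw values or residuals, and the threshold are not given, so two analysts following the same text could use different tests on the same outcome.

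The named fallback also fits the question poorly. The trial asks whether the combined regimen differs from sham and from each unilateral regimen, which calls for pairwise contrasts. Kruskal–Wallis only asks whether the four arms differ somewhere. No rank-based pairwise, paired or longitudinal method is named. Neither the parametric nor the rank comparison uses the baseline score as a covariate, although baseline is collected on everyone.

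**Working it through.** **Plan's own figure.** 60 / (1 − 0.20) = 75, rounded up to a multiple of 4 = 76, or 19 per arm (15 per arm without the dropout allowance). This reproduces. The starting 60 cannot be reproduced, because no effect size, SD or test is given. Everything below therefore rests on assumed inputs and is illustrative.

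**1. Does the undefined level of the check matter?** Simulated Shapiro–Wilk rejection at 0.05 (4,000 runs; distributions assumed):

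| Data | n = 15 | n = 19 | n = 60 | n = 76 |
|---|---|---|---|---|
| Bounded 0–66 score, 66 × beta(1.2, 2) | 12% | 16% | 73% | 87% |
| Lognormal, sigma 0.5 | 39% | 51% | 97% | 99% |

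If the check is run per arm and any flagged arm triggers the rank test (a rule the text does not state), the flag rates at 19 per arm are:
- normal data: 1 − 0.95^4 = 18.5%
- bounded score: 1 − 0.84^4 = 50%, against 87% pooled
- lognormal marker: 1 − 0.49^4 = 94%, against 99% pooled

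So the choice of level matters for a bounded score and hardly matters for a clearly skewed marker.

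**2. What does an omnibus rejection show?** Suppose all three active arms are 0.9 SD better than sham and the combined arm has no advantage over either unilateral arm. Kruskal–Wallis at 19 per arm then rejects in about 77% of 3,000 simulated trials. Rejection alone says nothing about combined versus unilateral.

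**3. Does the gate itself cost anything?** Skewed data: lognormal sigma 0.5, 19 per arm, baseline correlation r = 0.8 on the log scale, arm shifts 0, d/2, d/2, d, 2,000 runs. Omnibus power:

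| Method | d = 0.6 SD | d = 0.8 SD |
|---|---|---|
| Gated rule on post values | 42% | 69% |
| Always ANOVA on post values | 32% | 52% |
| ANOVA on change | 63% | 87% |
| Kruskal–Wallis on change | 76% | 94% |
| ANCOVA, not logged | 69% | 90% |

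On post values the gated rule does better than ungated ANOVA. With normal data the two are equal (31% and 31%; 52% and 52%). The size of the gated rule stayed near 5%. The gap between 42% and 69% at d = 0.6 reflects the use of baseline, since Kruskal–Wallis on change closes it.

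**4. What is baseline adjustment worth?** Assume normal data, unit SD, 19 per arm and shifts 0, 0.4, 0.4, 0.8. The mean shift is 0.4, and the squared deviations sum to 0.16 + 0 + 0 + 0.16 = 0.32. The noncentrality is 19 × 0.32 / v = 6.08 / v, where v = 1 for post values, 2(1 − r) for change and 1 − r² for ANCOVA. Power comes from the noncentral F with 3 and 72 df (71 for ANCOVA):

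| r | Post values | Change | ANCOVA |
|---|---|---|---|
| 0.5 | 6.08 → 50% | 6.08 / 1.00 = 6.08 → 50% | 6.08 / 0.75 = 8.11 → 63% |
| 0.6 | 50% | 6.08 / 0.80 = 7.60 → 60% | 6.08 / 0.64 = 9.50 → 71% |
| 0.8 | 50% | 6.08 / 0.40 = 15.20 → 90% | 6.08 / 0.36 = 16.89 → 93% |

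Simulation agrees within its error (change 51% to 90%, ANCOVA 62% to 93%). With only two time points, as for latency and BDNF, the group-by-time test equals ANOVA on change. Against that planned test, ANCOVA gains about 13 points at r = 0.5 and 3 at r = 0.8.

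The gain does not carry over to every kind of data. With skewed data, r = 0.6 and d = 0.6, the gated rule has 41% and unlogged ANCOVA 43%.

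**The case against.** A reader might infer that, once normality is rejected, the plan has no pairwise and no time-by-group analysis and so cannot answer its question. The text does not support that. Repeated measures ANOVA with its interaction is planned for the outcomes without any normality condition. The Bonferroni clause sits beside one-way ANOVA but is not expressly confined to it. Pairwise follow-up after Kruskal–Wallis is unspecified, not excluded, and corrected rank tests on change scores could answer the question. Naming the rank post hoc test is detail that a fuller protocol or SAP may hold.

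A reader might also infer that the pre-test inflates type I error or costs some 25 points of power. Size stayed near 5%. The power gap appears only when a rule on post values is set against a method that uses baseline, and the article does not say that Kruskal–Wallis is run on post values. Nor is the missing covariate peculiar to the rank branch, since the parametric branch lacks it too.

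These objections stand, and they limit the point to what is stated above. They do not remove it. The gate and its omnibus fallback are written into the plan, so this is something fixed badly rather than something left out.

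**Conclusion.** The point holds in limited form. A test on the trial's own data selects the between-group method under a rule that is not fully defined. The only named fallback is an omnibus test, while the question is pairwise. How the post hoc and repeated-measures steps apply after rejection is unclear, and no branch uses baseline as a covariate.

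The gate inflates no error rate and loses no power in the settings tried. The avoidable loss is from not adjusting for baseline. With normal data it ranges from slight (3 points against change scores at r = 0.8) to large (43 points against post values at r = 0.8). With skewed, unlogged data at r = 0.5 to 0.6, ANCOVA has no clear advantage over the rank test. The effect sizes, correlations and distributions are all assumptions, because the article gives none. Importance is low: a worthwhile improvement at almost no cost.

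**What to change.** Remove the Shapiro–Wilk test as a decision rule. For each primary outcome, prespecify one baseline-adjusted model: ANCOVA, or a mixed model where there are several visits. Use the log scale for BDNF, and for proBDNF and MMP-9 among the secondary outcomes. In each model name the three contrasts of combined against sham, low-frequency and high-frequency, under the Bonferroni correction already planned. Three named contrasts divide 0.05 by 3 within an outcome, where all six pairs would divide it by 6. Judge model fit on residuals, and keep rank methods on change scores as a sensitivity analysis.

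The cost is analysis wording only, with no new data, visits or patients. The change should be made before the analysis starts, since the Blinding section places unblinding at its end. One small downside is that serum effects are then reported as ratios of geometric means.

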### Sample size

We have calculated the sample size using the PASS 15 software. A literature search was conducted using FMA-UE as the primary indicator [8], specified as a two-sided test with *α* = 0.05 with a degree of certainty (test efficacy1-β) of = 0.8, and a total sample size of *N* = 60 cases was calculated. Considering a 20% dropout rate and the average distribution of each group, the total sample size was 76, with 19 individuals included in each group.

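### Within-arm paired t-tests stand among the efficacy analyses without being labelled descriptive, although they cannot separate a stimulation effect from background recovery

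*Protocol article*

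**What the plan says.** The Data analysis section of the protocol article opens by placing the efficacy analysis on an intention-to-treat footing and then lists its tests. Paired t-tests "will be used for pre- and post-treatment comparisons of groups". The same sentence assigns comparisons between arms to "one-way ANOVA for inter-group comparisons, and Bonferroni correction for post hoc comparisons between groups". The next adds: "Two-factor repeated measures ANOVA will be employed to investigate the impact of within-group factors (time points) and between-patient factors (subgroups) on outcomes", with main and interaction effects. One rule closes the section: a P "value of < 0.05 will be regarded as statistically significant". No test is named as the one that decides efficacy, and the paired tests are not restricted to description.

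The aim, at the end of the Background, concerns "significant changes in clinical behavioral assessments and cortical excitatory parameters in patients with convalescent stroke after 10 interventions with rTMS". That sentence goes on to set these changes against sham and one-sided stimulation, so the question is comparative. The Abstract and the Conventional treatment section give conventional rehabilitation to all four arms, and the inclusion criteria admit patients 30 to 180 days after stroke.

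**The concern.** A paired t-test in one arm asks whether that arm's mean change is zero. Patients in this window who receive two weeks of rehabilitation can be expected to improve whatever the coil does. The within-arm P value therefore measures recovery plus any stimulation effect, and it sets aside the comparison that randomisation provides.

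The risk is in interpretation. If the combined arm reaches P < 0.05 and sham does not, it is easy to report that the combined regimen works and sham does not. With small arms, identical true recovery can produce that pattern by chance. Because the paired tests share a section and a threshold with the between-arm tests, and none is named as decisive, nothing in the text rules that reading out.

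**Working it through.** **Inputs from the article.** Four arms at 1:1:1:1 (Randomization). In the Sample size section the calculation is "specified as a two-sided test with" alpha 0.05, "with a degree of certainty (test efficacy1-β) of = 0.8", with 60 patients before dropout, 20% dropout, and 76 in total (19 per arm).

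**The plan's own figure.** 60 / (1 − 0.20) = 75, and the next multiple of 4 is 76, or 19 per arm. The stated total is reproduced. The base of 60 cannot be checked, because the article gives no difference, SD or effect size. I use n = 19 per arm for everyone analysed and n = 60/4 = 15 for the number left after the planned dropout.

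**Assumed.** The standardised within-arm change, dz = mean change / SD of change, is not in the article, so it is varied from 0.3 to 1.2. The true dz is the same in all four arms, the arms are independent, and changes are normal.

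**Formulas.**
- Chance p that one arm's paired test is significant: two-sided 0.05 power from the non-central t with n − 1 degrees of freedom and non-centrality dz × √n.
- Combined significant and sham not: p(1 − p). This cannot exceed 0.25.
- Any mixed verdict among the four arms: 1 − p⁴ − (1 − p)⁴.

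**Worked case, n = 19, dz = 0.5.** Non-centrality = 0.5 × √19 = 2.18, which gives p = 0.541. Then p(1 − p) = 0.541 × 0.459 = 0.248, and 1 − 0.541⁴ − 0.459⁴ = 1 − 0.086 − 0.044 = 0.870.

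**Results, identical true change in all arms** (from unrounded p):

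| dz | p, n = 19 | Combined sig., sham not | Any mixed verdict | p, n = 15 | Combined sig., sham not | Any mixed verdict |
|---|---|---|---|---|---|---|
| 0.3 | 0.236 | 18% | 66% | 0.192 | 15.5% | 57% |
| 0.5 | 0.541 | 25% | 87% | 0.438 | 25% | 86% |
| 0.8 | 0.909 | 8% | 32% | 0.821 | 15% | 54% |
| 1.0 | 0.984 | 1.5% | 6% | 0.949 | 5% | 19% |
| 1.2 | 0.999 | 0.1% | 0.6% | 0.991 | 0.9% | 4% |

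**Contrast with a between-arm test.** In 20,000 simulated trials per setting (n = 15 and 19; dz 0.3, 0.5, 0.8 and 1.2), one-way ANOVA on the change scores was significant in 4.8% to 5.1% of trials throughout, as it should be when the arms do not differ. At n = 19 and dz = 0.5, 82% of trials had a mixed set of paired verdicts together with a non-significant ANOVA.

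**The case against.** The strongest reply is that the plan does not compare arms by paired tests. The sentence that names them gives comparisons between arms to ANOVA with Bonferroni, and the group-by-time interaction follows. That stands. A reader might infer that the trial will judge arms different when one paired test is significant and another is not, but no text says so. Nor does the order of the list make the paired tests the leading analysis: chi-square and Kruskal–Wallis come before them, and the section does not rank its tests. The shared 0.05 rule does not weaken the between-arm tests either, since the pairwise ones are Bonferroni-corrected and so stricter.

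The second reply is that the size depends on an unknown. That also stands. If rehabilitation produces large change in every arm, mixed verdicts become rare. The tests then mislead in another way: at dz = 1.2 sham itself is significant in at least 99% of trials. The 87% is also not the chance of the feared claim. It counts any disagreement, including sham significant and combined not. The relevant pattern stays at or below 25%.

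A reader might also count about 60 uncorrected paired tests: 10 outcomes × 4 arms at week 2, plus 5 clinical scales × 4 arms at week 6. The article does not support that as a planned number. It says only pre- and post-treatment, so a paired test to week 6 is an inference. It also checks normality first, and the Brunnstrom and Ashworth grades are ordinal. Sixty is an upper bound.

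Finally, baseline adjustment is not needed to cure the paired tests; relabelling them would do that. This is fair. I recommend the adjustment as a further gain from data already collected. That reporting weight is often left to an analysis plan is also true, but here the article itself states the tests, in its efficacy section and with a significance rule.

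**Conclusion.** The point holds in a limited form. The article lists within-arm paired t-tests among its efficacy analyses at P < 0.05 without calling them descriptive, and these tests cannot show a stimulation effect when all arms receive rehabilitation. Valid between-arm tests are planned alongside but none is named as decisive, so the damage is conditional on how the within-arm results are read.

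If they are misread, the false pattern of combined significant and sham not has a chance of 8% to 25% for dz from 0.3 to 0.8 with 19 per arm, falling to 1.5% at 1.0 and 0.1% at 1.2. These figures rest on equal true change, independent normal arms and an assumed dz. They do not support a statement that identical arms will usually look different whatever the outcome. Over the whole range, the within-arm P value does not answer the comparative question.

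**What to change.** In the Data analysis section, replace the paired t-test clause with a statement that change within each arm will be described by its mean and 95% CI, with no P value offered as evidence of efficacy. Then state that efficacy conclusions rest on the between-arm contrasts of combined stimulation with sham, low-frequency and high-frequency stimulation. Keep the Bonferroni correction as planned, and adjust for the baseline value of the outcome (ANCOVA in place of the unadjusted one-way ANOVA). Say what role the repeated measures ANOVA plays beside this.

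The cost is wording and some analysis work. Baseline values are already collected, and neither the sample size nor the visit schedule changes. What is lost is the set of within-arm P values.

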### Inclusion criteria

They will be recruited for the following criteria: (1) those with diagnosis in accordance with the relevant diagnostic criteria for cerebral infarction and cerebral hemorrhage in the “Chinese Guidelines for the Prevention and Treatment of Cerebrovascular Diseases” [21], confirmed by cranial CT or MRI to affect unilateral cerebral hemisphere; (2) disease duration of 30–180 days, and patients with stable vital signs, clear consciousness, and willingness to cooperate; (3) those with the first incidence of stroke; (4) those aged 30–75 years; (5) upper-limb Brunnstrom stages 2–5; and (6) patients and family members are willing to sign the informed consent form.

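### No baseline-adjusted arm contrast is named and no between-arm test is called decisive; one listed result, the repeated-measures group main effect, is diluted by including baseline

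*Protocol article*

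**What the plan says.** The Data analysis section of the protocol article assigns these roles to the tests of continuous outcomes:

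- Within each arm, before and after treatment: paired t-tests.
- Between arms: "one-way ANOVA for inter-group comparisons, and Bonferroni correction for post hoc comparisons between groups". No covariate is named, and the text does not say whether the dependent variable is the post-treatment value or the change.
- Time and group together: a two-factor repeated-measures ANOVA, to "analyze main and interaction effects".

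The section does not say which between-arm result decides the question.

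Under Study design, clinical, neurophysiological and serum measures are all taken at baseline and 2 weeks, and only the clinical measures are repeated at 6 weeks. So FMA-UE has three visits, and latency and BDNF have two. Eligibility covers "upper-limb Brunnstrom stages 2–5" and 30 to 180 days after stroke.

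The Sample size section gives power of 0.8 and a two-sided alpha of 0.05, and states that "a total sample size of *N* = 60 cases was calculated" before dropout. It states no effect size or SD.

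**The concern.** The trial's question is whether combined stimulation beats sham and each unilateral regimen. The only arm-versus-arm contrasts that the plan names are the Bonferroni contrasts, and these are attached to a one-way ANOVA without baseline. If that ANOVA is run on post-treatment scores, differences in severity that were already present at entry stay in the error term, although every patient's baseline value is on file.

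The group main effect has a different weakness. Treatment cannot have acted at baseline, so averaging that visit into each patient's mean pulls the arms together. A reader who took this main effect as the treatment effect would see it understated and tested with low power.

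The within-arm paired t-tests cannot separate treatment from recovery, since all four arms receive conventional rehabilitation.

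With several results for the same outcome and none named as decisive, the trial could report conflicting answers. At 15 completers per arm, the efficiency of the decisive test matters.

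**Working it through.** **Inputs from the document.** Four equal arms; alpha 0.05, two-sided; power 0.80; 60 patients before dropout, so 60/4 = 15 per arm; 20% dropout; 76 randomised.

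**The plan's own figure.** 15/(1 − 0.2) = 18.75, rounded up to 19 per arm, and 4 × 19 = 76. The dropout step reproduces. The 60 itself can be neither reproduced nor refuted, because no effect size or SD is given.

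**Assumptions.** r is the correlation between baseline and follow-up. It is not in the documents and is varied from 0.3 to 0.8. Also assumed: equal SDs, the same correlation between any two visits, 15 completers per arm, and an equal effect at both follow-ups. As a yardstick, take the effect at which a four-arm one-way ANOVA on post-treatment scores has 80% power with N = 60. The noncentral F distribution (3 and 56 df) gives Cohen's f = 0.44, with noncentrality λ = 60 × 0.4415² = 11.69. That the 60 was derived from such an ANOVA is not claimed.

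**Dilution of the group main effect.** The effect pattern over visits is (0, 1, 1) for FMA-UE, with mean 2/3, and (0, 1) for latency and BDNF, with mean 1/2.

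**Effective variance relative to the post-score ANOVA** (λ is divided by this):

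- ANCOVA: 1 − r². The precision lost by not adjusting is therefore r²: 9% at r = 0.3, 25% at 0.5, 49% at 0.7, 64% at 0.8.
- Change score: 2(1 − r).
- Main effect, three visits: [(1 + 2r)/3]/(2/3)². At r = 0.5 this is 0.667/0.444 = 1.50.
- Main effect, two visits: [(1 + r)/2]/(1/2)². At r = 0.5 this is 0.75/0.25 = 3.00.

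**Interaction.** Noncentrality is λ × (2/3)/(1 − r) with three visits (6 and 112 df) and λ × (1/2)/(1 − r) with two (3 and 56 df). With two visits it is the same test as the change-score ANOVA.

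**Power at f = 0.44, N = 60:**

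| Analysis | r = 0.3 | r = 0.5 | r = 0.7 | r = 0.8 |
|---|---|---|---|---|
| One-way ANOVA, post-treatment score | 80% | 80% | 80% | 80% |
| ANCOVA on baseline | 84% | 91% | 98% | 99.8% |
| Interaction, three visits | 67% | 84% | 98% | 99.9% |
| Interaction, two visits (= change score) | 64% | 80% | 96% | 99.6% |
| Group main effect, three visits | 72% | 61% | 52% | 49% |
| Group main effect, two visits | 37% | 33% | 29% | 28% |

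Simulation (3,000 runs each at r = 0.5, 0.7 and 0.8) agreed within about one percentage point for the post-score, change-score, ANCOVA and three-visit main-effect rows. The three-visit interaction also draws on week 6, whereas the ANCOVA row uses a single follow-up visit.

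**The case against.** The strongest reply is that the plan does use baseline. The group-by-time interaction is planned explicitly and compares the course from baseline between arms. At r of 0.7 or more it nearly matches ANCOVA, and at r = 0.8 with three visits it has 99.9% against 99.8%. This stands, so a reader should not infer that the between-arm tests ignore baseline altogether. It does not close the point. The interaction is not named as decisive, it does not yield an arm contrast at a stated visit, and at r = 0.3 its power (67% or 64%) is below that of the post-score ANOVA.

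Three further limits also stand.

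- A reader might infer that most of the precision is thrown away. That requires r² above one half, so r above 0.71, and no r is documented. Broad eligibility makes a sizeable correlation plausible for FMA-UE but says little about latency or BDNF.
- The one-way ANOVA could be meant for changes from baseline. The text leaves this open, so the post-score figures describe one possible reading.
- A reader might infer bias from chance baseline imbalance. Under randomisation that imbalance is part of the sampling error, and the unadjusted ANOVA remains valid.

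Nor does the plan say that the main effect or the paired t-tests will carry the efficacy claim. It lists them without ruling them out.

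**Conclusion.** The point holds as a matter of efficiency and of a comparison left unfixed. The stated arm contrasts come from a model without baseline, the decisive test is not identified, and one listed result, the group main effect, is diluted to 2/3 or 1/2 of the treatment effect. If the ANOVA is on post-treatment scores, the loss of precision runs from 9% to 64% as r goes from 0.3 to 0.8. For large samples ANCOVA is at least as precise as either the post-score or the change-score analysis at any r, so the recommendation does not depend on knowing r; only the size of the gain does. The power figures rest on the assumed correlation structure, equal SDs, 15 completers per arm and an equal effect at both follow-ups.

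**What to change.** Name one decisive between-arm comparison: week-2 FMA-UE on arm with baseline FMA-UE as covariate, by ANCOVA or an equivalent mixed model, and take the Bonferroni contrasts from that model. Analyse latency and BDNF in the same way, each with its own baseline. State that the repeated-measures group main effect and the within-arm paired t-tests are descriptive and will not be used as evidence of efficacy. The interaction can stay as a supporting analysis.

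The cost is wording only. Baseline values are already collected, no visit or patient is added, and the change can be made before unblinding.

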### Limitations and prospects

One limitation of this study is that it is a small sample trial and the follow-up duration is short. In the future, the sample size will be increased for multi-center trials, and the long-term effects of this scheme will be studied. In addition, because of the large inter-individual variation in cortical mapping, we relied only on surface markers to identify the target cortices, which may lead to localization bias. In the future, functional neuroimaging techniques (such as functional magnetic resonance imaging and functional near infrared spectroscopy) will be combined to guide further research.

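### Bonferroni over six pairs behind a significant ANOVA is valid but stricter than needed within each outcome; an F-protected Shaffer step-down, or simply Tukey-Kramer, recovers some power at little cost

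*Protocol article*

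**What the plan says.** The Data analysis section plans, for comparisons between arms, "one-way ANOVA for inter-group comparisons, and Bonferroni correction for post hoc comparisons between groups". It adds that a P "value of < 0.05 will be regarded as statistically significant". It does not give the number of pairs, does not state 0.05/6, and does not say that the pairs are tested only if the ANOVA is significant.

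The Randomization section fixes four arms at 1:1:1:1. The end of the Background names the comparisons of interest as the combined protocol against sham and against single-hemisphere stimulation, which is three of the six possible pairs.

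The Sample size section gives a calculation "specified as a two-sided test with *α* = 0.05", with power 0.8, a total of 60, and 76 after allowance for dropout. It reports no effect size or SD, only that "A literature search was conducted using FMA-UE as the primary indicator". Limitations and prospects concedes: "One limitation of this study is that it is a small sample trial".

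**The concern.** The pairwise tests answer the trial's question; the omnibus F test does not. With four arms there are 4 × 3 / 2 = 6 pairs, so a Bonferroni correction over all of them sets each threshold at 0.05/6 = 0.0083. That divisor guards against all six nulls being true at once. If the pairs are examined only after the ANOVA has rejected that very configuration, the guard is no longer needed and the divisor is larger than error control requires.

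What is at stake is power for the comparisons between arms, in a trial that expects about 15 evaluable patients per arm. The validity of the results is not at stake.

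**Working it through.** **The plan's own figure.** "Considering a 20% dropout rate", 60 / (1 − 0.20) = 75, rounded up to a multiple of four = 76, or 19 per arm. This reproduces. The 60 itself cannot be reproduced without an effect size. Solving backwards for a four-arm F test (α = 0.05, power 0.80, N = 60) gives Cohen's f ≈ 0.441. If one arm alone differs by d SD, f = d√3/4, so d = 0.441 / 0.433 = 1.02. This d is an assumption derived from the stated N, not a figure in the protocol.

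**Why six is too many after the F test.** For four means, the number of pairwise nulls that can be true together is 6 (all equal), 3 (three equal), 2 (two and two), 1 or 0. Rejecting all-equal leaves at most 3. Under the six-pair rule, the chance of a false rejection is then at most 3 × 0.0083 = 2.5%.

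**The alternative.** After a significant F test, order the six P values and test them at 0.05/3 (four times), 0.05/2 and 0.05, stopping at the first failure. Each threshold is at least 0.05/6, so with the same gate this rule rejects every pair that the planned rule rejects. No simulated trial contradicted this.

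**Simulated family-wise error within one outcome** (normal data, equal variances, n = 15 per arm):

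| Truth | ANOVA, then Bonferroni/6 | ANOVA, then step-down |
|---|---|---|
| All arms equal | 3.8% | 4.8% |
| One arm very different | 2.2% | 4.3% |
| Two arms against two | 1.7% | 4.9% |

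**Simulated power** (true means in SD units, in the order combined, low-frequency, high-frequency, sham):

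| True means | n per arm | Target | Bonferroni/6 | Step-down | Gain (points) |
|---|---|---|---|---|---|
| 1.02, 0, 0, 0 | 15 | combined v sham | 52.5% | 61.2% | 8.7 |
| 1.02, 0, 0, 0 | 19 | combined v sham | 66.5% | 74.4% | 7.9 |
| 1.02, 0, 0, 0 | 15 | all three combined contrasts | 28.3% | 38.8% | 10.5 |
| 1.02, 0, 0, 0 | 19 | all three combined contrasts | 43.5% | 54.9% | 11.4 |
| 1.02, 0.51, 0.51, 0 | 15 | combined v sham | 51.7% | 56.4% | 4.7 |
| 1.02, 0.51, 0.51, 0 | 19 | combined v sham | 65.6% | 69.7% | 4.1 |

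**Range over other assumptions.**
- One arm different by 0.8 to 1.2 SD: 5.4 to 8.8 points per pair, worth 13 to 18% more patients.
- Two arms against two at f = 0.44: 9.3 to 9.7 points.
- Graded pattern: 2.3 to 4.8 points for combined versus sham (6 to 9% of n), and 4.6 to 8.4 points for combined versus a single-hemisphere arm, from a base power of only 10 to 22%.

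**Simpler rules.** Holm over six pairs after the F test gains 0.3 to 4.2 points per pair. Tukey-Kramer lowers the critical t at 56 df from 2.74 to 2.65. For combined versus sham it gains about 3 to 4 points in the tabulated settings; in the graded one it reaches 56.0% (n = 15) and 69.6% (n = 19), almost the same as the step-down.

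**The case against.** The strongest reply is that nothing here is wrong. ANOVA followed by Bonferroni is standard, valid and available in the named software. That stands: the point is about efficiency only.

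Second, six pairs and a formal gate are inferred. If the family is the three comparisons in the Background, Bonferroni is already 0.05/3. At n = 15 with one arm different by 1.02 SD, ungated tests at 0.05/3 give 62.9% for combined versus sham against 61.2% for the step-down, and 39.1% under both rules for all three contrasts. The gain vanishes. If the ANOVA is not a gate, it is also no longer exactly true that the step-down rejects everything the plan rejects. Both limits stand.

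Third, the largest gains assume that the single-hemisphere arms equal sham. The protocol's discussion of the stimulus protocol reports benefit from single-sided stimulation and favours the combination over it, which suggests a graded pattern and smaller gains. This stands too, and is why a range is given.

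A reader might also infer three stronger things that the documents do not support:
- *That the plan pays for multiplicity twice.* The gate itself costs little: 52.7% ungated against 52.5% gated in the one-arm setting, and about 1 point at most elsewhere. The loss comes from still dividing by six afterwards.
- *That the strict correction protects nothing.* There are three primary outcomes, and the article states no correction across them. If outcomes were independent, the chance of at least one false pairwise claim over three would be 1 − (1 − 0.022)³ = 6.5% under the planned rule and 1 − (1 − 0.043)³ = 12.4% under the step-down with one arm different; with two against two, 5.0% and 14.0%. The slack does limit trial-level error, though it was not designed to.
- *That the gain is a general 8 to 10 points, or 17% more patients.* The 17% is the squared ratio of the differences detectable with 80% power at 0.05/6 and 0.05/3, (1.312 / 1.213)² = 1.17. It describes one threshold at one power and does not carry over to the graded pattern.

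**Conclusion.** The point holds as a cheap improvement. On the natural reading of six pairs behind a significant ANOVA, the planned correction is valid but uses less than half of its 5% allowance within an outcome when one arm, or two of the four, truly differ (about 1.7 to 2.3%). The F-protected Shaffer step-down holds 5% and gains about 2 to 10 points per pair, depending on pattern, effect size and pair; Tukey-Kramer gains about 3 to 4 for combined versus sham.

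These figures rest on normal data with equal variances, 15 or 19 evaluable per arm, and assumed effects, because the protocol reports none. They apply within one outcome at one time point.

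**What to change.** State the family of comparisons in the Data analysis section, then choose one rule.

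- **All six pairs, simplest:** replace Bonferroni with Tukey-Kramer tests and simultaneous 95% intervals. Its intervals agree with its tests.
- **All six pairs, more power:** if the four-arm F test is significant at 0.05, test the ordered pairwise P values at 0.05/3, 0.05/3, 0.05/3, 0.05/3, 0.05/2 and 0.05, stopping at the first that fails.
- **Only the three combined-arm comparisons:** say so, and use Holm over those three without a gate. With the combined arm alone different by 1 SD and 19 per arm, power per pair is 81%, against 64% for the planned rule over six pairs.

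The cost is one sentence and no new data; the unadjusted P values are the same. The article places unblinding at the end of the data analysis, so the change can be made and dated while the group codes are still masked.

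There are two downsides. Step-down decisions can disagree with Tukey intervals reported beside them: in the settings examined, about 18 to 25% of trials with any significant pair had one whose Tukey interval included zero. And none of these rules controls error across the three primary outcomes; that needs its own statement, preferably made at the same time.
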